#### Self-reported data

At enrollment and at the beginning of each subsequent season, all participants complete a brief survey with questions about socio-demographic characteristics that are not available in the EMR, occupational responsibilities, health status, and KAP regarding seasonal influenza vaccination.

At the end of each influenza season, participants are asked to complete another brief survey that includes questions about their overall health and to describe previously unreported illnesses (‘End-of-season survey’). Surveys are designed to be self-administered electronically through the Internet using the REDCap system.

#### Work absenteeism

During active surveillance, we document days of missed work associated with respiratory illnesses. Missed workdays are identified by self-report (as part of acute illness and illness follow-up SMS messages) and by periodic reviews of human resource department employee absentee records. Illness days are identified as all days between self-reported illness onset and illness resolution dates (from SMS surveillance messages or by direct phone screening). Thus, missed work due to illness includes days that participants directly reported missing due to illness and days of absence (according to employee records) between the illness onset and resolution dates.

### Laboratory methods

#### Nasal specimens

When participating HCP report being ill with a respiratory illness during the influenza season, they are instructed to self-collect a nasal swab using a self-swabbing kit [31] that includes illustrated instructions, a nasal mid-turbinate swab, and a tube with room temperature transport medium. Respiratory specimens are placed in viral transport medium and delivered to the respective hospitals from HCP’s residences by a courier service or are hand-carried by participants to study staff at their respective hospitals. If participants prefer not to collect the nasal swab themselves, study staff are able to collect it for them.

#### Molecular diagnostics

Specimens from Beilinson Hospital are stored at 4 °C and delivered by courier to the Clinical Virology Laboratory (CVL) at Soroka University Medical Center twice a week, where they are immediately aliquoted and frozen at − 80 °C. Specimens from participating Soroka University Medical Center HCP are brought to the laboratory daily, where they are aliquoted and frozen.

After one freeze-thaw cycle, specimens are tested for influenza A viruses [A(H1N1)pdm09 and A(H3N2)], influenza B viruses, respiratory syncytial virus (RSV), human metapneumovirus, and coronaviruses (NL63, 229E, OC43, HKU1) using validated multiplex quantitative real-time reverse transcription polymerase chain reaction (mqRT-PCR) assays [32], with protocols, primers, probes, and reagents supplied by Hy-labs (Israel) and Integrated DNA Technologies (USA). The CVL, in collaboration with the University of Michigan (Ann Arbor, Michigan, US), has completed the World Health Organization and US CDC influenza proficiency panels. Quality Control for Molecular Diagnostics (Glasgow, Scotland, UK) proficiency panels were also completed for influenza, RSV, human metapneumovirus (hMPV) and coronaviruses.

Some specimens will have molecular characterization with genetic sequencing and other assays to detect genetic markers to determine viral subclades and antiviral resistance at a reference laboratory approved by the study steering committee. Remaining aliquots of all study specimens may be sent to a US CDC-designated facility (also approved by the study steering committee) for additional virus characterization, banking, and storage. No specimens will contain personal identifiers.

##### Blood Specimens

At enrollment, prior to each influenza season, 10 mL specimens of whole blood are collected from all participants. In addition, 5 mL specimens of whole blood are collected at the end of season 1 and the start and end of subsequent seasons. Participants who received the influenza vaccine during the study period will be asked to provide an additional sample of 5 mL of whole blood approximately 28 days (within a range of 21–42 days) after vaccination. Sera are extracted from whole blood and stored frozen until testing.

Participants who consent to providing additional blood at enrollment, as an optional part of the study, provide an additional 10 mL heparinized whole blood at enrollment and the end of season for extraction of peripheral blood mononuclear cells (PBMC). In addition, we collect 10 mL of heparinized whole blood approximately 7 days after vaccination from participants who agree to this optional part of the study. All PBMC samples are centrifuged, undergo cell count, diluted to 1-5 × 10^6^ cells/ml and gradually frozen to − 80 °C, and placed in liquid nitrogen within 24 h. PBMC samples will be used for cell-mediated immunity assays.

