**Methods:**

Cohort enrollment began in October, 2016; a second year of the study and a second wave of cohort enrollment began in June 2017. The study will run for at least 3 years and will follow approximately 2000 HCP (who are both employees and members of Clalit Health Services [CHS]) with routine direct patient contact. Eligible HCP are recruited using a stratified sampling strategy. After informed consent, participants complete a brief enrollment survey with questions about occupational responsibilities and knowledge, attitudes, and practices about influenza vaccines. Blood samples are collected at enrollment and at the end of influenza season; HCP who choose to be vaccinated contribute additional blood one month after vaccination. During the influenza season, participants receive twice-weekly short message service (SMS) messages asking them if they have acute respiratory illness or febrile illness (ARFI) symptoms. Ill participants receive follow-up SMS messages to confirm illness symptoms and duration and are asked to self-collect a nasal swab. Information on socio-economic characteristics, current and past medical conditions, medical care utilization and vaccination history is extracted from the CHS database. Information about missed work due to illness is obtained by self-report and from employee records. Respiratory specimens from self-collected nasal swabs are tested for influenza A and B viruses, respiratory syncytial virus, human metapneumovirus, and coronaviruses using validated multiplex quantitative real-time reverse transcription polymerase chain reaction assays. The hemagglutination inhibition assay will be used to detect the presence of neutralizing influenza antibodies in serum.

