#### Timeline of enrollment

A total cohort of 2000 HCP will be enrolled over a three-year period. Enrollment periods are targeted prior to influenza seasons. During Year 1 of the study, which targeted the 2016/2017 influenza season, enrollment could not begin until October 6, 2016 due to funding and institutional approval delays. Recruitment continued until the start of the influenza season (December 4, 2016) for a total of 8 weeks. This recruitment period included a month of frequent Israeli national holidays (October 2016), during which enrollment was challenging because many HCP were on vacation. In Year 1 of the study, 596 HCP were enrolled, and will contribute to Years 1, 2 and 3 of this 3-year cohort study. Enrollment in Year 2 began in June 2017. New enrollees in Year 2 will contribute to Years 2 and 3 of the study.

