#### Electronic medical records

Information on socio-demographic characteristics, current medical conditions, medical history, medical care utilization, and influenza vaccination history are extracted from the CHS EMR at enrollment and at the end of each study year. For all participants, chronic medical conditions are identified using a combination of the International Classification of Diseases, Ninth Revision (ICD-9) codes from inpatient and outpatient records, International Classification of Primary Care Coding (ICPC), physician-entered free text diagnoses from outpatient medical records, and electronic chronic disease registries maintained by the Clalit Research Institute (details in Additional file 1: Annex 1 and Annex 2).

Routine influenza vaccine administration for CHS HCP members who receive the vaccine is recorded in the health fund’s EMR. Because the vaccine is offered free of charge for members in CHS hospitals and clinics, nearly all of those who are vaccinated do so in such settings. Participants are considered vaccinated for a specific season if they received influenza vaccine from September 1 through March 31 of the relevant influenza season. To date, influenza vaccine has not been offered in Israel prior to September 1. We document prior vaccine history, according to EMR records, from the the 2006–2007 season, 10 years prior to the first year of our study.

In addition, we document medical visits for ARFI during weeks of active surveillance in every study year. We also document medically attended ARFI in the 10 years prior to enrollment, distinguishing between medical visits that occurred during the influenza season and those that occurred outside of the influenza season. Medically attended ARFI episodes during active surveillance and for years prior to enrollment are captured through evaluation of outpatient visits, emergency room visits, and hospital admissions. Criteria used for medically attended ARFI are described in Additional file 1: Annex 3.

Outpatient visits, emergency room visits, medications dispensed at CHS pharmacies, and hospital admissions are regularly updated in the CHS EMR, making it possible to document medical visits nearly in real-time by recording ICD-9 codes and free text entered by physicians. We also access the EMR to document influenza antiviral medications and antibiotics dispensed during acute illnesses.

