#### Data analysis of immunogenicity

Since distributions of HI titer data are typically highly left-skewed, all statistical analyses will be conducted using log base-2 transformed titer data; results are then back-transformed to the original scale for ease of interpretation [28, 41]. Pre- and post-vaccine draws are assumed to be correlated within each person, thus repeated measures linear mixed models will be fitted to estimate geometric mean titers (GMT) and geometric mean ratios (GMR). Compound symmetric covariance error structures will be assumed for repeated measures within individuals. GMT will be calculated by back-transforming the least squares mean estimates of logged titer data. GMR will be calculated by back-transforming the difference of least squares means of post-vaccination and pre-vaccination logged titer estimates. GMR will be interpreted as the geometric mean fold ratio of post-vaccination titer to pre-vaccination titer. Multivariate estimates adjusted a priori for age and sex. Linear, quadractic, and cubic terms for age will be examined to consider possible nonlinear associations with age. Other covariates (e.g., education, household size, working in a hospital setting) may also be adjusted within multivariable models if they were associated with the number of prior vaccinations and either preseason GMT or post-vaccination GMR among vaccines.

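### For early-summer Year 2 enrollees the pre-vaccination titer may be two to three months old or more at the dose, and the GMR analysis neither limits nor models that gap, so waning could mimic blunting from repeated vaccination

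*Protocol article*

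**What the plan says.** All places are in the protocol article.

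- **Baseline draw (Blood Specimens):** "At enrollment, prior to each influenza season, 10 mL specimens of whole blood are collected from all participants".
- **Further draws (same section):** "5 mL specimens of whole blood are collected at the end of season 1 and the start and end of subsequent seasons". The abstract's Methods paragraph is shorter: "Blood samples are collected at enrollment and at the end of influenza season", plus one draw a month after vaccination for those vaccinated. It names no start-of-season draw.
- **Post-vaccination draw (Blood Specimens):** "approximately 28 days (within a range of 21–42 days) after vaccination".
- **Enrolment timing (Timeline of enrollment):** Year 1 ran from October 6 to December 4, 2016. For the next wave, "Enrollment in Year 2 began in June 2017".
- **Vaccine timing (Electronic medical records):** "To date, influenza vaccine has not been offered in Israel prior to September 1". A dose counts for a season if given "from September 1 through March 31 of the relevant influenza season".
- **Intended baseline (Sample size for immune response):** serum is to be taken before vaccine becomes available. No limit is put on how long before.
- **Analysis (Data analysis of immunogenicity):** "GMR will be interpreted as the geometric mean fold ratio of post-vaccination titer to pre-vaccination titer". Adjustment fixed in advance is for age and sex. Other covariates may enter if they are associated with the number of prior vaccinations and with either preseason GMT or GMR.

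**The concern.** GMR is a ratio, so its denominator should be the titer just before the dose. If blood is drawn months earlier and the titer falls in the meantime, the measured baseline is too high and the fold rise too low. The same fall in everyone would shift all GMRs alike and leave comparisons intact. The difficulty arises if the fall depends on recent vaccination. A person boosted the previous winter may still be losing antibody in summer, while a person with a low, flat titer has little to lose. The assay floor points the same way: a titer below 10 is set to 5 (Hemagglutination inhibition assay), so someone already at the floor cannot show a decline.

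At stake is the third objective, whether repeated vaccination modifies immunogenicity. An error that lowers GMR mainly in recent vaccinees has the same sign as the blunting the study is looking for. Fold rises from the first seasons of Year 1 and Year 2 enrollees may also not be comparable, because their draw-to-dose gaps can differ by months.

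**Working it through.** **1. The plan's own timing figure.** October 6 to December 4, 2016 is 59 days, or 8.4 weeks. This agrees with the 8 weeks stated for Year 1 recruitment. A Year 1 draw was thus at most 59 days before December 4. Table 2, note c, says nationwide vaccination was already under way, so the gap to a dose could be short.

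**2. Gap for Year 2 enrollees.** The day in June is not given, so both ends of the month are used. September 1 is the documented earliest dose date. Mid-October is an assumed dose date. December 4 is the Year 1 season-start date carried over to 2017.

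| Draw (2017) | to Sept 1 | to Oct 15 | to Dec 4 |
|---|---|---|---|
| June 1 | 92 days | 136 days | 186 days |
| June 30 | 63 days | 107 days | 157 days |
| July 31 | 32 days | 76 days | 126 days |

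A June draw is 2.1 to 3.0 months before the earliest dose. For a draw at the end of July this shrinks to about one month.

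**3. Which sample is the baseline?** The sentence on further draws has two readings.
- If season 1 is the 2016/17 study season, Year 2 enrollees also give a start-of-season sample in 2017.
- If it is each participant's first season, which fits the abstract, their enrolment sample is the only one before the dose.

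The first reading does not guarantee a usable sample either. The article dates the start of the 2016/17 season to December 4, after vaccination had begun, and does not tie the start-of-season draw to vaccine availability.

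**4. Effect on GMR.** The article gives no waning rate, so titer half-lives of 6, 12 and 24 months are assumptions. For gap g and half-life h in months, the baseline is too high by g/h on the log2 scale, and

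observed GMR = true GMR × 2^(−g/h).

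| Gap | h = 6 | h = 12 | h = 24 |
|---|---|---|---|
| 2 months | 0.79 | 0.89 | 0.94 |
| 3 months | 0.71 | 0.84 | 0.92 |
| 4.5 months | 0.60 | 0.77 | 0.88 |

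For example, 3/6 = 0.5 and 2^(−0.5) = 0.71. In participants with flat titers the factor is 1. If only a fraction f of the recent vaccinees have the gap, the group's log2 shift is f × g/h.

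**5. Could this alone give a significant contrast?** Take two equal groups totalling n, a two-sided 5% test, an assumed SD of 1.5 for the log2 fold rise, a 3-month gap in everyone, and waning in one group only. The standard error is SD × √(4/n). The chance of a significant result in the blunting direction is Φ((g/h)/SE − 1.96), nominally 2.5%. The article cites earlier serology subgroups of 300 to 800.

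| n | SE | h = 6 | h = 12 | h = 24 |
|---|---|---|---|---|
| 300 | 0.173 | 82% | 30% | 11% |
| 800 | 0.106 | 99.7% | 65% | 22% |

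Milder inputs (2-month gap, h = 24, n = 300, SD 2.0) give 5.5%. These figures suppose that every participant has the gap, so they are upper cases for a mixed cohort.

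**6. Would the stated covariate rule catch it?** Not reliably. A covariate enters if it is associated with the number of prior vaccinations and with preseason GMT or GMR. The gap depends on when a person enrolled and was vaccinated, and need not be related to prior vaccinations. The distortion comes from the product of gap and recent vaccination, which a screen of main effects can miss.

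**The case against.** Four points weigh on the other side.

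- **Design choice.** Drawing before vaccine is available is deliberate. The late Year 1 start shut out people already vaccinated that season, and earlier enrolment avoids that selection. This stands. The point is not that June enrolment was a mistake, but that the analysis should allow for the gap it creates.
- **A later sample may exist.** Returning Year 1 participants, and Year 2 enrollees in Year 3, have start-of-season draws, and nothing suggests these fall in June. This stands and limits the point to the first season of new summer enrollees. Whether those enrollees also have a later sample is the ambiguity described above.
- **A condensed article.** A draw window or an interval covariate may be in the full protocol or in Annex 7, which is not shown, and the covariate list is left open. This lowers confidence. But the article does fix a post-dose window, a covariate screen and a post-over-pre measure, and as stated these leave the baseline interval unbounded.
- **No waning data.** The share of enrollees drawn in June or July, the waning rate and any excess waning in recent vaccinees are all absent from the article. Unvaccinated staff infected the previous winter could wane too. This stands, and is why the size is given only as a range.

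A reader might infer that the Year 2 baseline is months out of date throughout, that the third objective is therefore biased, or that detection of infection by a 4-fold rise in unvaccinated staff is impaired. The article supports none of these. The long gap applies to early-summer enrollees vaccinated that autumn. The bias is conditional on differential waning. The third objective also covers antibody landscape and cell-mediated response. And many unvaccinated participants may have little titer to lose.

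**Conclusion.** The point holds in conditional form. The dates establish that a June 2017 enrolment draw is at least 63 to 92 days before any dose, with no stated upper limit on the gap and no interval term named in the GMR model. The direction follows from the ratio: a baseline taken before further waning is too high, so GMR is too low, and more so in the group that wanes more. If that group is the recent vaccinees, the result can mimic or exaggerate blunting. The size is not established. Under the assumed half-lives, a 3-month gap gives factors from 0.92 (small) to 0.71 (material) in waning participants, and the effect on a group contrast shrinks with the share who have the gap. Comparisons of post-vaccination GMT are not affected. This merits a change because the possible error lies in the direction of the study hypothesis and the remedy is inexpensive.

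**What to change.** 1. State which sample supplies the pre-vaccination titer, separately for new and returning participants, and use the latest available sample before the dose. Reconcile the Blood Specimens section with the abstract on whether new enrollees give a start-of-season sample.
2. Add to the GMR model the interval from pre-vaccination draw to vaccination and its interaction with prior-season vaccination. Specify both terms in advance rather than leaving them to the covariate screen.
3. Add a sensitivity analysis restricted to pairs with a short interval, for example a pre-vaccination draw within 60 days before the dose.

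The cost is two more model terms and fewer pairs in the restricted analysis. No new data should be needed: the vaccination date comes from the medical record (Table 3), and both the 48-hour exclusion rule and the 21 to 42 day window already require enrolment and draw dates to be tracked. The 60-day limit would leave out June draws altogether, since the shortest June gap is 63 days, unless a later pre-dose sample exists. The number of pairs retained should therefore be reported.

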#### Hemagglutination inhibition assay

The hemagglutination inhibition (HI) assay will be used to detect the presence of influenza antibodies in serum. HI to inactivated influenza vaccine components and influenza circulating strains will be performed at a reference laboratory using standard methods [33] as described previously [28, 34] (See Additional file 1: Annex 4). Egg-grown viruses will be supplied by the US CDC’s International Reagent Resource. Preparation of serum samples will include (a) treatment with a receptor-destroying enzyme to remove nonspecific inhibitors, and (b) removal of nonspecific agglutinins by serum adsorption with packed red blood cells (RBC). Standard 0.5% turkey RBC will be prepared for influenza A (H1N1)pdm09 antigens and ether-treated B influenza antigens. Given indications that neuraminidase of circulating antigenic clusters of influenza A(H3N2) viruses (since 2014) have acquired the ability to bind to RBC, modified HI assays will be conducted for influenza A(H3N2) antigens using guinea pig red blood cells in the presence of the antiviral oseltamivir carboxylate, which inhibits influenza neuraminidase. Serum will be diluted 2-fold starting from 1:10. The HI titer will be the reciprocal of the serum dilution in the last well with complete HI. The geometric mean titer from duplicate results will be reported; HI < 10 will be considered 5 for the purposes of statistical analyses.

#### Additional immunological assays

Additional serologic testing may occur, including neuraminidase inhibition assay testing, antigen microarray testing [35] and other approaches. Neuraminidase-specific antibodies have been shown to play a role in protection against influenza infection [36, 37]. However, many questions remain about the role of neuraminidase in vaccine effectiveness [38].

### Attitudes toward morbidity due to influenza and other respiratory illnesses

As a sub-study within this project, approximately 15–25 in-depth open-ended qualitative interviews are conducted each year with participants who recently had a wintertime respiratory illness and agree to participate in this sub-study.

Participants are contacted by phone approximately 1 week after confirmation of respiratory illness resolution and asked to participate in an interview. Interviews cover topics including illness experience, including symptoms, duration, perceived severity, and disruption to their daily activities and responsibilities, perceptions of how the illness impacted work responsibilities, perceptions of how the illness impacted life outside of work, and reasons for choosing to receive or not receive the influenza vaccine this season (see Additional file 1: Annex 5). Interviews will be recorded by audio recorder and later transcribed. After transcription, the data are translated from Hebrew to English and qualitatively analyzed using NVivo Software (QSR International, Melbourne, Australia) to identify themed code-words that may point to common patterns of comments across the interviews.

